### Sample size estimation

Using a pretrial power analysis, we determined that a minimum sample size of 37 patients was required for correctly detecting a within-group improvement of 5.5 on the BBT, if such a difference truly exists, with a two-sided significance level of 5% and a power of 80% [51]. The number of 5.5 blocks had previously been reported as the smallest real difference between two measurements for the affected upper limb [41]. Since the minimally clinically important difference on BBT is, to our knowledge, not established yet, we made the assumption that the smallest real difference would be perceived by stroke patients as being of clinical relevance for their daily life. After adjusting for: (a) a case-fatality rate of 8% as reported at 1 year post stroke in a Danish nationwide population-based study [52] and (b) a 20% loss of participants at follow-up for other reasons, we estimated that 51 participants were needed in each group [53]. Hence, the total sample size is 102 participants.

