### Statistical analysis

Background characteristics will be compared between the intervention groups with *t* tests (continuous variables) or chi-squared tests (categorical variables). The development of both primary and secondary outcome variables will be analyzed in longitudinal models over the stroke recovery trajectory (baseline, post-intervention and 6-month follow-up), and the difference of the outcomes between the two intervention groups at each of the study time points will be analyzed in multivariable linear regression models. Analyses will be adjusted for the stratification variables (sex and the ability to perform finger extension). Possible differential attrition is adjusted for by weighting the outcomes that are available at each of the study time points with the inverse of the probability of being present; these probabilities are estimated in logistic regression models including all background characteristics and outcomes at previous study time points. To account for this weighting and for repeated observations on the same individual generalized estimating equations (GEE) methods are used to adjust the variance of the parameter estimates. Analyses are performed with SAS version 9.4. The statistical significance level is 5%.

Additional file 3 shows the SPIRIT Checklist [55, 56] for this study protocol.

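### With about 75 participants at 6 months and estimated weights, the usual GEE sandwich variance would run the nominal 5% BBT test at roughly 6% to 10%; a small-sample correction should be stated

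*Protocol article*

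**What the plan says.** In the Statistical analysis section of the protocol article, each available outcome is weighted by the inverse of the estimated probability that the participant is present at that time point. On the weight model it says: "these probabilities are estimated in logistic regression models including all background characteristics and outcomes at previous study time points". On how inference allows for the weights and for repeated observations it says: "generalized estimating equations (GEE) methods are used to adjust the variance of the parameter estimates". The outcome models adjust for sex and finger extension, the software is SAS 9.4 and the significance level is 5%. The article names no form of the GEE variance, no reference distribution and no small-sample correction, and it does not say how variable the weights are expected to be.

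The Sample size estimation section starts from "a minimum sample size of 37 patients was required". It then allows for "a case-fatality rate of 8% as reported at 1 year post stroke" and for "a 20% loss of participants at follow-up for other reasons", and arrives at 51 per group.

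**The concern.** The standard GEE empirical variance puts squared residuals in place of the unknown variances. Residuals of participants who pull the fit towards themselves are too small. A participant with a large weight pulls harder and also counts more in the variance sum. The estimator is therefore biased downwards in modest samples, and the bias grows as the weights become more unequal. A logistic model with many terms and few missing participants makes the weights unequal even when its covariates have nothing to do with dropout.

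The primary 6-month BBT comparison and the 6-month secondary comparisons share this method. If the standard errors are too small, the confidence intervals are too narrow and a p-value just under 0.05 is not a 5% result.

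**Working it through.** **1. The plan's own sample size.** Inputs from Sample size estimation: 37, 8%, 20%. 37 / (0.92 x 0.80) = 37 / 0.736 = 50.3, rounded up to 51 per group, 102 in total. This reproduces the stated figure. The 37 itself cannot be checked, because no SD is given, but nothing below depends on it.

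**2. Participants at 6 months.** 102 x 0.736 = 75.1 present and 102 - 75.1 = 26.9 missing. The 8% is a one-year rate. With no deaths at all by 6 months, 102 x 0.80 = 81.6 would be present.

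**3. Size of the weight model.** The list of variables in Trial setting and participants gives 28 items when each named variable is counted once. Outcome measures gives nine measures per time point: BBT, FMA-UE, grip, three pinch strengths, touch threshold, pain and mRS. For presence at 6 months with two earlier time points, 28 + 9 + 9 = 46 terms at one term each, against about 27 missing participants. The article does not fix the coding, so the number of terms is varied below.

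**4. False-positive rate with an uncorrected sandwich and a normal reference.** Three separate simulations (A: 5,000 null trials per cell; B and C: 3,000) used 102 randomised participants, about 27 missing and weights estimated by logistic regression. A analysed a weighted linear model with group, sex and finger extension, and an outcome floored at zero. Rejection rates in %:

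| Weight covariates | A | B | C |
|---|---|---|---|
| none | 5.6 | 6.2-6.4 | 5.9 |
| 10 | 5.7-6.8 | 6.1-6.2 | 6.8 |
| 20 | 6.7-7.3 | 7.3-7.8 | 7.4 |
| 30 | 8.1-8.6 | 8.2-8.4 | 8.7 |
| 38 | 9.2-9.7 | 9.1-9.7 | 7.3 |
| 46 | not run | 6.8-8.7 | 6.6 |
| 55 | not run | not run | 6.5 |
| leverage-corrected sandwich | 3.9-5.0 | 4.1-5.0 | 3.8-5.0 |

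Monte Carlo error is about 0.3 to 0.5 points per cell. The corrected rows of A and B use a t reference. In A, a t reference alone lowered the rates by only 0.3 to 0.6 points.

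The rate does not keep rising with the number of covariates. Once the logistic model separates, every retained participant has a fitted probability near 1, the weights collapse to about 1 and the test returns towards its unweighted size. In C, 29% of fits separated at 38 covariates, 80% at 46 and 99% at 55. In B, about 83% separated at 46.

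**5. Other settings.** A wider grid of single-time models (5 to 35 covariates, weak to strong dropout prediction) gave 5.8% to 9.7%. A weighted GEE over all three time points gave 5.2% to 8.5%. Settings with very strong dropout prediction and a very prognostic dropout score gave 10.0% to 10.7%. With 10% loss (102 x 0.90 = 91.8 present), the three-time-point GEE gave 4.6% to 6.7%.

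**6. Cross-check through the standard errors.** In the main grid the sandwich SE was 0.84 to 0.98 of the true SE. If the statistic is otherwise normal, the actual level is 2 x [1 - Φ(1.96 x ratio)]:

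- ratio 0.98: 2 x [1 - Φ(1.921)] = 5.5%
- ratio 0.84: 2 x [1 - Φ(1.646)] = 10.0%

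This agrees with the simulated range, so the excess comes from standard errors that are too small.

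**The case against.** **The article does not say that the variance is uncorrected.** This is correct. The form of the sandwich and the choice between z and t are details that a journal article may leave to a fuller document. A reader might infer that the plan specifies an uncorrected variance; it does not. What stands is that the article fixes both ingredients of the problem: an all-inclusive weight model, and GEE variance as the whole answer to the weighting, at about 75 participants. Someone applying the text as written would most likely use the usual empirical estimator.

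**The weights may not be heavy, and the error may be smaller than feared.** A reader might infer that participants are heavily weighted and that the test runs at up to 12%. The documents give no weight distribution, and the calculations do not support that reading. In B the median effective sample size was 62 to 76. One further set of runs gave 11.5% to 11.6% with an effective sample size of 41 at 38 covariates, but A, B and C did not reproduce either figure. The cross-check formula gives about 12% at the SE ratio of about 0.79 seen in the extreme settings, yet the rate counted directly there was 10.0% to 10.7%.

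**Treating estimated weights as known is conservative and could cancel the bias.** The simulations estimated the weights and then treated them as fixed, so both effects are in the figures. They do not cancel in general: most weighted cells with about 27 missing lie above 5%, by up to about 5 points.

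**The weight model is the real cause.** This stands in large part. Without weights the sandwich costs only about one point, and the rest comes from the weights. A corrected variance does not make the weights useful: where the logistic model separates, attrition is left unadjusted whatever the standard error. That is a separate issue.

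**Conclusion.** The point holds conditionally. If the weighted analysis uses the usual empirical variance with no small-sample correction, the nominal 5% test of the 6-month BBT runs at roughly 6% to 10%. Where it falls in that range depends on how many terms enter the weight model, how strongly they predict dropout and how near-separated fits are handled. At the literal count of 46 terms the figure is 6.6% to 8.7%. Without weights it is about 6%, and with 10% loss it is near 5%.

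This rests on the article's planned attrition of about 26%, a linear outcome model adjusted for the stratification factors, weights treated as fixed, and assumed dropout mechanisms that the documents do not give. The direction and the effect of the correction were consistent across the simulations; the exact level is not a property of the plan.

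**What to change.** Add one sentence to the Statistical analysis section: inference from the weighted GEE models uses a bias-corrected empirical variance (for example Mancl-DeRouen or Morel-Bokossa-Neerchal), with a t reference on contributing participants minus regression parameters. The alternative is a bootstrap that resamples participants and refits both the weight model and the outcome model each time. The simulations tested a Mancl-DeRouen-type leverage correction; the other two options were not simulated here. The analyst should confirm that the chosen SAS procedure offers the correction together with weights. Keep the correction even if the weight model is shortened, since the unweighted test is already slightly above 5%.

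The cost is a software setting and wider intervals. Taking the main-grid SE ratios, intervals of the right width would be 1/0.98 = 1.02 to 1/0.84 = 1.19 times as wide as the uncorrected ones. No new data or participants are needed. The size of the weight model and its separation need a decision of their own.

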## Discussion

To our knowledge, this is the first trial investigating the effect of multiple sessions of ESS treatment in the acute stroke phase on the recovery of upper limb paresis. Several studies have shown that the process of upper limb recovery, and especially that of hand dexterity, is most pronounced during the first 4 weeks post stroke after which the recovery gradually levels off before reaching a plateau around 6 months post stroke. Therefore, initiation of rehabilitation in the early weeks post stroke may be essential for achieving successful upper limb recovery at the end of the rehabilitation process. Our trial intends to evaluate the effect of ESS – a rehabilitation method with the potential of applicability in clinical practice. ESS is easy to administer, inexpensive, free of patient discomfort and probably highly acceptable to frail patients in the early days post stroke.

Contrary to previous studies that primarily focused on the stimulation of the peripheral hand nerves at wrist level, we use two sets of large electrodes (see “Intervention” section) to stimulate somatosensory receptors in the shoulder, elbow and wrist regions. We believe that the larger area covered may be beneficial, but because we do not have a third trial arm receiving ESS at wrist level only, we will not be able to identify the effect of increasing the stimulation areas per se.

The eligibility criteria for participation in this trial are very broad. Basically, we include all adult stroke patients living in the hospital’s catchment area, except those with remaining upper limb paresis from a previous stroke, contraindications to ESS, severe prestroke disability or inability to provide informed consent. Based on this nonrestrictive participant selection, the results can be generalized to the larger population of patients with a first-ever stroke or successful recovery after a previous stroke and who present an upper limb paresis of varying degrees of severity. However, since our trial is not powered to perform subgroup analyses, we may encounter challenges in detecting the effect of ESS in such a heterogeneous sample. The possibility of overlooking a treatment effect on a specific subgroup of stroke patients (type II error) is a limitation of the study.

Designing the control ESS treatment was challenging since the intervention can be perceived by the trial participants who may also interact with each other during hospitalization. Since a completely inactive ESS treatment gave rise to concerns about high dropout rates in the control group, we designed a sham ESS treatment with an extremely low treatment dose. It is unlikely that the total amount of sham ESS treatment (1.2 min) is sufficient to induce any training effects. However, we are unable to verify this since we do not have a trial arm receiving completely inactive or no ESS. As a consequence, our trial results can be biased towards an underestimation of the effect of ESS treatment. It is noteworthy that both the control and the intervention group receive the same amount of attention from the personnel during the ESS sessions. Although some participants might figure out their group allocation, we hope that they would be motivated to continue in the trial due to fact that they are offered upper limb training in addition to the usual rehabilitation.

## Trial status

The recruitment of participants was initiated on 13 October 2014 and will continue until complete sample size is achieved which is expected in March 2017. At the submission time of this protocol article, patients are still being recruited for the trial.

## Abbreviations

ADLs: Activities of daily living
ES: Electrical stimulation
ESS: Electrical somatosensory stimulation
mRS: Modified Rankin Scale
OT: Occupational therapy/occupational therapist
PT: Physiotherapy/physiotherapist
